#### 7.4 Sample size

The sample size is estimated before the study with the use of nQuery Advisor software. Our preliminary study of IgA nephropathy showed that the three-year rate of the primary endpoint (doubling of serum creatinine, end-stage renal disease, and death) among patients with IgA nephropathy taking RAS inhibitors was 36%. It is estimated that MMF treatment will reduce this rate to 16%. Thus, the enrollment of 76 per group will provide the study with a statistical power of 80% at a two-sided significance level of 0.05. Considering 10% of participants lost to follow-up over 3 years, the final sample size was 84 per group.

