## **Laboratory evaluation**

Laboratory evaluation of all specimens will be performed according to visit procedure.

Renal endpoints that need determined by serum creatinine including doubling in serum creatinine, kidney failure have to be confirmed by two measurements at least 4-weeks apart. For this purpose, patients may need to attend an unscheduled visit one month after the study visit.

Laboratory values that exceed the boundaries of a notable laboratory abnormality should be evaluated by the investigator and additional evaluations should be performed if judged appropriate by the investigator. If the laboratory abnormality is the primary reason for an unforeseen hospitalization or otherwise fulfills the criteria for a Serious Adverse Event, then the procedure for notification of serious adverse events must be followed. Likewise, if the laboratory abnormality leads to discontinuation from the study or from treatment, then the patient must be followed until the abnormality resolves or until it is judged to be permanent.

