## **9 Management and reporting of adverse events/adverse reactions**

### **Definitions**

#### **Adverse event (AE)**

Any untoward medical occurrence in a patient with the use of a medical product and which does not necessarily have to have a causal relationship (association) with this product. An AE can therefore be any unfavorable and unintended sign (including an abnormal laboratory finding), symptom, or disease temporally associated with the use of the product, whether or not related to the product.

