## 3. Study Design

This study is a prospective, open-label, randomized controlled, blinded endpoint (PROBE) trial. This trial will include participants with IgA nephropathy who are at a high risk of disease progression.

Patients with IgA nephropathy were recruited at the renal division of Nanfang Hospital, Southern Medical University. After recruitment, the patients first entered into a 12-week run-in period, during which the patients were treated with comprehensive supportive care, including blockade of RAS using maximum tolerable daily dose of losartan to reduce blood pressure to a target below 130/80 mmHg and a urine protein excretion (UPE) below 0.75g per day. The participants were also advised for lifestyle modification, including quitting smoking, restricting high-salt intake, and avoiding nephrotoxic drugs. Anemic patients with a hemoglobin level lower than 110g/L were treated with erythropoietin. Statin was used when necessary. Dietary sodium intake were monitored by urinary sodium excretion rate (or chloride excretion rate in patients treated with sodium bicarbonate) measured by 24-hour urine sample.

The patients who were tolerable to losartan (<30% eGFR decline and without hyperkalemia) and proteinuria (0.75-3.5 g/day) at the end of run-in period were randomized to receive MMF plus supportive care or supportive care alone. The MMF plus supportive care group received a daily oral dose of 1.5g MMF for the first 12 months, followed by a maintenance daily dose of 0.75g to 1.0g for at least 6 months. Both MMF plus supportive care and supportive care alone group stayed on supportive care as in the run-in period. All participants were followed up at regular intervals for 3 years.

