### **6.4. Safety Analysis**

The analysis of safety endpoints will be performed on the SS. For safety analysis, no formal hypothesis testing will be performed. Descriptive analysis will be performed to summarize safety events. Serious adverse events and adverse events will be summarized as the number of events and the number (%) of patients experiencing at least one event. Differences in the proportions of patients experiencing at least one event will be tested using Fisher's exact test.

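### SAP 6.4 compares SAEs between arms only in total, primary-outcome events included, so an MMF kidney benefit could dilute an excess of other SAEs; add a row without those events (minor)

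*Combined protocol and SAP*

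**What the plan says.** **Analysis.** SAP 6.4: "Serious adverse events and adverse events will be summarized as the number of events and the number (%) of patients experiencing at least one event". The proportions with at least one event are then compared by Fisher's exact test; SAP 4.4 sets two-sided p < 0.05, unadjusted, for safety. The same paragraph of 6.4 also says that there will be no formal hypothesis testing.

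**What counts as an event.** Protocol section 9: "An AE can therefore be any unfavorable and unintended sign (including an abnormal laboratory finding), symptom, or disease", whether or not related to the product. Death and inpatient hospitalization make an event serious. The hospitalization exceptions cover stays under 12 hours, admissions planned before the study and admissions not associated with an AE; none names a study endpoint. Protocol 7.10, Laboratory evaluation, comes directly after the rule for confirming creatinine endpoints with this: "If the laboratory abnormality is the primary reason for an unforeseen hospitalization or otherwise fulfills the criteria for a Serious Adverse Event", SAE notification must be followed.

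**Other safety summaries.** SAP 6.4.1 separately lists AEs of special concern (blood count changes, sepsis, gastrointestinal symptoms, certain infections, hepatic dysfunction, malignancy) and study-drug-related SAEs. No kidney endpoint is on the special-concern list.

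**Who is counted, and when.** SAP 3.7.1 runs the AE window from first MMF use to 30±7 days after last use. Protocol section 9, Collection, does not require AEs or SAEs to be documented in a patient who has not used MMF. Protocol 7.12 and SAP 5.2 tie the safety set to use of the study drug or study medication. Table 1 in both documents, however, schedules AE/SAE collection from Visit 3 onward without distinguishing arms.

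**The concern.** A kidney or cardiovascular death is both a primary-outcome event and an SAE. So is an unplanned admission to start dialysis. The protocol expects such outcomes to be much rarer with MMF. A single all-SAE proportion therefore adds an efficacy difference in one direction to any toxicity difference in the other. If MMF protects the kidney and also causes, say, serious infections, the total can show little difference although the non-kidney SAEs differ. At stake is how the all-SAE line is read, which is the one line that does not depend on a judgement of relatedness or on a list of known reactions.

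**Working it through.** **The plan's own figure first.** Protocol 7.4: "the enrollment of 76 per group will provide the study with a statistical power of 80% at a two-sided significance level of 0.05", for 36% vs 16% over 3 years. With pooled variance and no continuity correction,

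n = [1.960·√(2·0.26·0.74) + 0.842·√(0.36·0.64 + 0.16·0.84)]² / 0.20² = (1.216 + 0.508)² / 0.04 ≈ 74.3, so 75 per group, against 76 stated.

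Inflation: 76 × 1.1 = 83.6, so 84, as stated: "Considering 10% of participants lost to follow-up over 3 years, the final sample size was 84 per group". The inputs 36%, 16% and 84 per arm are used below.

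**Assumptions, not in the documents.**
- Other (non-endpoint) SAEs: 10% control, 20% MMF, a true excess of 10 points.
- f: share of endpoint patients whose endpoint is also recorded as an SAE.
- The two kinds of event are independent within an arm.
- Control-arm events are collected over the same period as MMF-arm events.

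**Formula.** All-SAE proportion = 1 − (1 − other rate)(1 − f × endpoint rate).

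**Three-year window (endpoints 36% vs 16%).**

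| f | Control | MMF | Difference (points) |
|---|---|---|---|
| 0 | 10.0% | 20.0% | +10.0 |
| 0.25 | 1 − 0.90 × 0.91 = 18.1% | 1 − 0.80 × 0.96 = 23.2% | +5.1 |
| 0.5 | 1 − 0.90 × 0.82 = 26.2% | 1 − 0.80 × 0.92 = 26.4% | +0.2 |
| 0.75 | 34.3% | 29.6% | −4.7 |
| 1 | 42.4% | 32.8% | −9.6 |

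**On-drug window.** Table 1 shows the last dispensing at week 78. Adding about 30 days gives (78 × 7 + 30)/365 ≈ 1.6 years. Assume this window for both arms and a constant hazard:
- Control: 1 − 0.64^(1.6/3) = 21.2%.
- MMF: 1 − 0.84^(1.6/3) = 8.9%.

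| f | Control | MMF | Difference (points) |
|---|---|---|---|
| 0.25 | 14.8% | 21.8% | +7.0 |
| 0.5 | 19.5% | 23.6% | +4.0 |
| 0.75 | 24.3% | 25.3% | +1.0 |

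Maintenance MMF is for at least 6 months, so the real window may lie between the two.

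**Fisher's test.** Exact power, 84 per arm, two-sided 0.05, for a larger assumed excess of 25% vs 10%: 67% with endpoint events excluded. With them included it is 27% (f = 0.25) and 8% (f = 0.5) over 3 years, or 41% and 21% over 1.6 years.

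**Excess needed to cancel out.** For assumed control rates of other SAEs between 5% and 20%, the 3-year totals are equal when the true MMF excess is about 4 to 5 points (f = 0.25) or 9 to 10 points (f = 0.5).

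**The case against.** 1. **Other tables show the harm.** Infections and cytopenias would largely appear in the special-concern rows, drug-related SAEs are summarized apart, and SAP 6.3.1 reports the composite and its components by arm. This largely stands: only the all-SAE total is affected. But relatedness is a yes/no judgement by investigators who know the assignment and means little in the control arm, and the special-concern list covers known reactions only.

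2. **f has no source.** This stands. The 36% is a rate of creatinine doubling or ESRD in the protocol abstract, with death added in 7.4. A confirmed doubling is a laboratory criterion that may need only an unscheduled visit. A reader might infer from the lower rows of the 3-year table that the total would reverse in favour of MMF. That needs f of 0.75 or more in this scenario, which nothing in the documents supports.

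3. **The direction is not certain.** A reader might infer that the total always flatters MMF. Read literally, SAP 3.7.1 and 5.2 and protocol 7.12 and section 9 leave control-arm events uncollected or outside the safety set, and the bias could then run against MMF. Table 1 and the between-arm comparison in SAP 6.4 point the other way. This stands as a condition on the whole point.

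4. **Harm read only from the reduced table would mislead.** This stands. It would discard kidney and cardiovascular deaths and confirmed loss of kidney function even if MMF contributed, and total SAEs by arm is a legitimate net measure.

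5. **The safety analysis is called descriptive.** True, although Fisher's test is named. A descriptive table shows the same diluted difference, so power is only a secondary yardstick.

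**Conclusion.** The point holds as a minor reporting gap. Counting endpoint deaths and unplanned endpoint admissions as SAEs follows from the definitions and from the absence of any exemption; no passage states it outright. If both arms are counted over a comparable period and MMF has the planned effect, the all-SAE total understates an excess of other SAEs. Under the stated assumptions, a 10-point excess shows as +5.1 or +0.2 points over 3 years, and +7.0 or +4.0 over 1.6 years, at f = 0.25 or 0.5. For the proportion with at least one AE of any kind the effect is probably small, since most patients may have one anyway. The documents do not support saying that drug harm would go unseen in the safety report as a whole.

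**What to change.** Add to SAP 6.4: SAEs and AEs are shown by arm (a) in total and (b) excluding events that the blinded adjudication committee has classified as components of primary outcome 1 or 2, and admissions for those events. The two are interpreted together, and deaths and the total remain visible in every presentation.

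Before that comparison can be made, reconcile protocol 7.12 (safety set), protocol section 9 (Collection), SAP 3.7.1 and SAP 5.2 with Table 1 and SAP 6.4, so that AE documentation, window and safety set are defined the same way for both arms.

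Cost: a few table rows and a link from each AE record to the adjudication result. The added rows need no new data, provided that control-arm AEs are collected as Table 1 schedules. The downside is two SAE figures per arm in place of one.

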#### **6.4.1. Adverse events**

The number, frequency and incidence of the following AEs will be summarized,

1. AEs with special concern include drug-related AEs listed by the pharmaceutical company of the study drug, including leukopenia or leukocytosis, sepsis, gastrointestinal symptoms (diarrhea, stomachache, vomiting, anepithymia), certain types of repeated infections (pneumonia, influenza syndrome, urinary tract infection, herpes zoster, etc.), hepatic dysfunction or transaminase elevation, malignancy.
2. SAEs, study drug-related SAEs, and AEs leading to study withdrawal.

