| Efficacy assessments | 
 
1. Composite outcomes of a doubling of serum creatinine, ESRD, or death due to kidney or cardiovascular cause
 
2. Time to progression of chronic kidney disease
 
3. The time to 30% reduction in eGFR from the baseline.
 
4. Annual absolute changes in the eGFR (eGFR slope) over the trial period.
 
5. Rapid eGFR decline (<math>< -5</math> ml/min/1.73m^2/year).
 
6. Percentage change in the rate of urinary protein excretion at the end of trial over the baseline.
 
                                                                                                                                   |
| Safety assessments   | 
All adverse events (AEs), serious adverse events (SAEs), study drug-related SAEs, AEs leading to study withdrawal, AEs leading to study withdrawal, and AEs related to the study drug
                                                                                                                                                                                                                                                                                                                                                                                                                                                                                                                        |

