**Safety endpoints**

1. Including all adverse events (AEs), serious adverse events (SAEs), study drug-related SAEs, AEs leading to study withdrawal, and AEs related to the study drug occurred during the study period will be recorded.
1. SAEs were defined as death, life-threatening conditions, requiring inpatient hospitalization or prolongation of existing hospitalization.
2. AEs with special concern were defined as drug-related AE listed in the drug information provided by the pharmaceutical manufacture of MMF, including leukopenia or leukocytosis, anemia, sepsis, gastrointestinal symptoms (diarrhea, stomachache, vomiting, anepithymia), certain types of repeated infections (pneumonia, influenza syndrome, urinary tract infection, herpes zoster, etc.), hepatic dysfunction or transaminase elevation, malignancy.

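### SAP 6.4.1 leaves out two safety rows that the protocol names: anemia as an event of special concern, and all adverse events related to the study drug

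*Combined protocol and SAP*

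**What the plan says.** **Protocol.** Section 7.7 (Safety endpoints) defines the special-concern events by reference to the MMF manufacturer's drug information and then names them, "including leukopenia or leukocytosis, anemia, sepsis, gastrointestinal symptoms" and so on through repeated infections, hepatic events and malignancy. The same section gives the general categories. After all AEs, SAEs and drug-related SAEs it continues: "AEs leading to study withdrawal, and AEs related to the study drug occurred during the study period will be recorded". The safety row of the Abstract likewise ends "and AEs related to the study drug".

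**SAP.** Item 1 of 6.4.1 opens "AEs with special concern include drug-related AEs listed by the pharmaceutical company of the study drug" and continues "including leukopenia or leukocytosis, sepsis, gastrointestinal symptoms (diarrhea, stomachache, vomiting, anepithymia". Item 2 reads in full: "SAEs, study drug-related SAEs, and AEs leading to study withdrawal". The parent section, 6.4, makes a general commitment: "Serious adverse events and adverse events will be summarized as the number of events", together with the number and percentage of patients affected. Section 6.4.2 covers laboratory measures by time point and treatment group. Section 7, which should record departures from the planned analysis, reports none.

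**The concern.** The SAP decides which safety tables are produced. If it is followed as written, two rows that the protocol sets out are not prespecified, and the reader of the results is not told why.

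The anemia row matters because two causes overlap here. By the protocol's own account anemia is on the study drug's list. It is also managed in every participant as part of supportive care: erythropoietin is given below 110 g/L (protocol 7.3). A named event row is the direct way to show whether anemia is reported more often with MMF. The row for drug-related AEs matters because it reports the investigator's causality judgment on non-serious events, which an overall AE count does not show.

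**Working it through.** No figure in the plan needs recomputing. The check is a comparison of lists.

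**1. Special-concern list (protocol 7.7 against SAP 6.4.1, item 1)**

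| Group | Protocol | SAP |
|---|---|---|
| Leukopenia or leukocytosis | yes | yes |
| Anemia | yes | **no** |
| Sepsis | yes | yes |
| Gastrointestinal | yes | yes |
| Repeated infections | yes | yes |
| Hepatic | yes | yes |
| Malignancy | yes | yes |

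The protocol has seven groups and the SAP six; 7 − 6 = 1, and the missing one is anemia. The order and the examples in brackets are otherwise the same.

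**2. General categories (protocol 7.7 against SAP 6.4 and 6.4.1)**

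| Category | Where the SAP covers it |
|---|---|
| All AEs | 6.4 |
| SAEs | 6.4 and 6.4.1, item 2 |
| Drug-related SAEs | 6.4.1, item 2 |
| AEs leading to withdrawal | 6.4.1, item 2 |
| Drug-related AEs of any seriousness | in part only: manufacturer-listed events (item 1) and drug-related SAEs (item 2) |

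Four of five are covered explicitly and the fifth in part. The data for the fifth are planned: the protocol (section 9, Collection) requires relationship to product for each AE, and SAP 3.7.1 defines the adverse reaction by a yes/no judgment. No SAP table uses that class.

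**3. Which events lose their own row**

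- An anemia AE that is not serious and does not lead to withdrawal is counted in the overall AE summary, but no row names it.
- A non-serious AE judged related, not on the manufacturer's list and not leading to withdrawal, is also in the overall summary, but nothing shows that it was judged related.

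**4. Whether other planned outputs replace the rows**

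- The overall AE count cannot isolate either class.
- Hemoglobin is a safety laboratory variable (SAP 3.7.2). SAP 6.4.2 plans summaries by time and arm, mean plots, a mixed model and listings of clinically significant results. Its first sentence speaks of the screening visit, but its second paragraph is plainly longitudinal and by arm. This is real information on anemia, but mean hemoglobin is not a count of events. If one arm has more anemia, more of its patients qualify for erythropoietin; to the extent that this raises hemoglobin, the difference in means narrows.

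**5. Whether an anemia row could be filled in both arms**

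- Protocol section 9 (Collection) says AEs need not be documented as such while a patient has used no MMF.
- SAP 3.7.1 runs the AE window from first MMF use to 30±7 days after the last.
- Protocol 7.12 limits the safety set to patients who used the study drug; SAP 5.2 excludes those who took no study medication.
- Table 1 in both documents schedules AEs/SAEs from Visit 3 onward with no distinction by arm, and SAP 6.4 plans Fisher's exact test on proportions of patients with events, which presupposes two groups.

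Read literally, the first three leave the control arm without AE data; the last item assumes that it has them. Table 1 schedules hematology at every visit after randomization, regardless of arm. Protocol 7.10 (Hematology) also mentions 3-monthly intervals, so the exact frequency is not settled, but the measurement is planned in both arms.

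**The case against.** The best case for the SAP has four parts.

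- **Anemia is one example in an open list.** The SAP's governing phrase is the manufacturer's list, and by the protocol's account anemia is on it, so an anemia row is permitted. This stands as far as it goes. But the row becomes discretionary, and SAP 4.1 lets the study team combine or exclude cells with counts below 10 when they are found. Naming the row removes that discretion.
- **The events are still reported.** A reader might infer from the gaps that two protocol safety endpoints go unreported, or that the hemoglobin data go unused. The documents do not support either reading. Anemia is a component of the special-concern definition, not an endpoint of its own; SAP 6.4 covers all AEs; 6.4.1 covers part of the drug-related class; and 6.4.2 analyses hemoglobin by arm.
- **The protocol promises recording, and its section 7.12 leaves table content to the SAP.** This is fair. It makes the difference an unexplained narrowing and not a breach. Section 7 of the SAP was still the place to explain it.
- **A restored row may have no control-arm data.** This stands, and it limits what the fix can deliver. It would be wrong to assume that everything needed is already collected. Drug-related AEs are also mainly a description of the MMF arm, since controls receive no MMF.

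**Conclusion.** The point holds in a limited form. The SAP omits the anemia row and a row for all drug-related AEs, both named in the protocol, and gives no reason. What is lost is the prespecified separate display of these events; they still enter the overall AE summary, and hemoglobin is still analysed. The documents give no basis for saying how many events are affected, or that the safety conclusion would look more favourable as a result.

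The conclusion rests on reading SAP 6.4.1 as the working list of AE tables and on the absence of any explanation in SAP section 7. It concerns completeness of safety reporting and does not touch the primary analysis. It should be corrected, because neither the overall count nor mean hemoglobin substitutes for the missing rows.

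**What to change.** 1. In SAP 6.4.1, item 1, restore anemia so that the list matches protocol 7.7.
2. In item 2, add AEs related to the study drug, serious and non-serious. No line for all AEs is needed there, because SAP 6.4 already provides it.
3. If either omission was deliberate, state the reason in SAP section 7.
4. Before the anemia row is presented as a comparison of arms, reconcile protocol section 9 (Collection), SAP 3.7.1 and the safety-set definitions (protocol 7.12, SAP 5.2) with Table 1. State whether control-arm AEs are documented and analysed, and over what window. Until that is settled, compare the arms on anemia only through the scheduled hemoglobin data.
5. Optionally, show beside the anemia row the number of patients who start erythropoietin after randomization, by arm, from the concomitant-medication records that Table 1 schedules at every visit. This is an aid to interpretation, not something the protocol requires.

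Items 1 and 2 cost one word and one table line, using AE data that the plan already requires wherever AEs are documented. Item 4 costs more if control-arm AEs have not been documented, since wording alone cannot supply them.

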### **1. Prior and concomitant medication**

Any diagnoses/diseases/event terms documented in the following forms will be coded using the latest Medical Dictionary for Regulatory Activities (MedDRA) version:

2. Co-morbidities (medical history, concomitant diseases)
3. Adverse events

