## **7.12 Data analysis**

### **Statistical considerations**

All statistical details including calculated variables and proposed format and content of tables will be detailed in the Statistical Analysis Plan (SAP). The SAP will be finalized before study database lock. The SAP will be kept as a stand-alone document.

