### **4.4. Multiplicity Adjustment**

For the primary analysis, a two-sided p value of <0.025 was regarded as statistically significant. For the secondary and safety analyses, no multi-test adjustment was employed, and a two-sided p value of <0.05 was regarded as statistically significant. The outcomes are clearly categorized by degree of importance (primary, secondary) and a limited number of subgroup analyses are pre-specified.

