#### 6.4.2. Laboratory Examination

Lab examination includes blood hematology, blood biochemistry, urine analysis during the screening visit. Descriptive analysis will be performed to summarize the results and clinical significance judgment of lab examination. For blood hematology, blood biochemistry, urine analysis, listings of patients with clinical significance results will be provided. The listings will be presented according to the subject ID, sex, age, date of test, examination index, examination result and/or clinical evaluation.

All measures will be summarized by use of standard measures of central tendency and dispersion using mean and standard deviation as well as quartile points at 0.25, 0.5 and 0.75 where appropriate stratified by measurement time points and by treatment group. Longitudinal mean plots will be used to display means and 95% confidence bands over time by randomized group. To assess the treatment effect on laboratory variables, a linear mixed effects model with a random intercept by subject and with treatment, time (categorical) and a treatment by time interaction as fixed effects will be used. The effect of the treatment will be assessed as the adjusted mean difference and its 95% confidence interval.

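### Leukopenia and leukocytosis are listed as one adverse event of special concern, and neither the protocol nor the SAP requires a separate count of leukopenia

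*Combined protocol and SAP*

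**What the plan says.** SAP 6.4.1 opens with the commitment "The number, frequency and incidence of the following AEs will be summarized". Its first entry is the set of events of special concern, "including leukopenia or leukocytosis, sepsis, gastrointestinal symptoms" and so on, in which the two white-cell findings form a single item between commas. The safety endpoints in protocol 7.7 carry the same joint item: "including leukopenia or leukocytosis, anemia, sepsis, gastrointestinal symptoms". (The protocol list also contains anemia, which the SAP list omits; that is a separate matter.)

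SAP 6.4 says that events are summarised as the number of events and the number and percentage of patients with at least one. It adds: "Differences in the proportions of patients experiencing at least one event will be tested", by Fisher's exact test. SAP 4.4 sets the level: "For the secondary and safety analyses, no multi-test adjustment was employed, and a two-sided p value of <0.05 was regarded as statistically significant".

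Three other provisions bear on the point:

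- Protocol 7.11 says that adverse event terms "will be coded using the latest Medical Dictionary for Regulatory Activities (MedDRA) version".
- Protocol 7.12 leaves the format and content of tables to the SAP. The SAP contains no table layout for adverse events.
- SAP 6.4.2 plans patient listings, summaries by arm and time point, and, for laboratory variables, "a linear mixed effects model with a random intercept by subject and with treatment, time (categorical) and a treatment by time interaction".

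**The concern.** A low and a high white-cell count are opposite findings. Leukopenia is the first event named in the special-concern list. Leukocytosis can come from an infection, which can occur in either arm, and the same list includes repeated infections.

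If one figure covers both, a reader cannot tell which direction produced it. If leukocytosis is about as frequent in both arms, it adds a balanced background to an unbalanced event, pulls the relative risk towards 1, and makes the between-arm test less likely to show the leukopenia difference.

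**Working it through.** The plan states no figure on this point, so there is none to reproduce. The check has two parts: what the text fixes, and how much a joint count could matter.

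**What the text fixes.** SAP 6.4.1 applies its summary to the listed events, and SAP 6.4 counts patients with at least one event. Applied literally to an item that reads leukopenia or leukocytosis, a patient with either change counts once. Neither document states a separate count, a direction or a laboratory threshold for the item. Neither states expressly that the two are to be summed.

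**Illustration.** Inputs:

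- 84 patients per arm, from protocol 7.4.
- Two-sided level 0.05, from SAP 4.4; Fisher's exact test, from SAP 6.4.
- Leukopenia in 12% (MMF) and 2% (control): assumed.
- Leukocytosis at the same rate in both arms, independent of leukopenia, from 0% to 10%: assumed.
- Both arms enter the safety comparison in full: assumed.

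Joint proportion = 1 − (1 − leukopenia) × (1 − leukocytosis). With leukocytosis at 10%:

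- MMF: 1 − 0.88 × 0.90 = 0.208
- Control: 1 − 0.98 × 0.90 = 0.118
- Relative risk: 0.208 / 0.118 = 1.76
- Risk difference: 0.208 − 0.118 = 0.090

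Power is exact, from enumerating all pairs of binomial counts with 84 per arm.

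| Leukocytosis, both arms | Joint item, MMF vs control | Relative risk | Risk difference | Fisher power |
|---|---|---|---|---|
| 0% (same as leukopenia alone) | 12.0% vs 2.0% | 6.0 | 10.0 points | 65% |
| 1% | 12.9% vs 3.0% | 4.3 | 9.9 points | 59% |
| 2% | 13.8% vs 4.0% | 3.5 | 9.8 points | 53% |
| 5% | 16.4% vs 6.9% | 2.4 | 9.5 points | 41% |
| 10% | 20.8% vs 11.8% | 1.8 | 9.0 points | 28% |

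**Unequal leukocytosis.** Take leukopenia at 10% vs 1% (power 65% alone) and let the two events occur in different patients, so that the rates add:

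- Leukocytosis 2% on MMF and 8% on control: joint item 12% vs 9%, power 6%.
- Leukocytosis 8% on MMF and 2% on control: joint item 18% vs 3%, power 89%.

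A joint count can therefore hide the contrast or enlarge it. In neither case does the figure say which change drove it.

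**The case against.** A reader might infer that the plan adds the two changes in one table row, so that a leukopenia signal will be diluted and the trial will understate this harm. The documents do not support that.

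- **No table and no summing rule.** SAP 6.4.1 is a prose list of what counts as special concern. On the same reading, the gastrointestinal symptoms, or hepatic dysfunction and transaminase elevation, would each be one row, and nothing says so. This stands against the stronger claim. It does not supply a commitment to separate counts.
- **MedDRA coding.** Coding lets the events be tabulated by term. That makes a split possible, but neither document requires one.
- **The laboratory route.** White-cell count is a study haematology variable, and Table 1 schedules haematology at every visit after randomisation. SAP 6.4.2 plans listings that show each result, quartiles by arm and time, and a mixed model. This is a real but partial safeguard. A listing is not a count by arm, and a mean can conceal opposite shifts. The section also opens by referring to the screening visit only, although its analysis by time and arm would make no sense on that restriction.
- **Attribution.** The SAP describes the special-concern events as drug-related. If that means attributed by the investigator, leukocytosis from an infection might not be counted at all. If it means named in the manufacturer's information, it would be. The text does not settle which.
- **The size is assumed.** No rates are given, the risk difference hardly moves, and SAP 6.4 calls the safety analysis descriptive before naming Fisher's test. Power is therefore illustrative only.
- **Control arm.** SAP 5.2 excludes participants who took no study medication, SAP 3.7.1 runs the adverse event window from first to last MMF use plus 30±7 days, and the Collection part of protocol section 9 does not require events before any MMF use to be documented. Whether controls enter the comparison is unclear, and that is a larger question than this one.

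These points limit the claim. None of them yields an incidence of leukopenia by arm.

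**Conclusion.** The point holds as a gap in specification. Both documents list two opposite white-cell changes as one item of special concern, and neither requires leukopenia to be counted separately. Counted as written, the item cannot show direction and can mask a leukopenia difference.

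Under the assumed 12% vs 2%, equal leukocytosis of 5% to 10% takes the relative risk from 6.0 to between 2.4 and 1.8, and power from 65% to between 41% and 28%. The absolute difference falls only from 10.0 points to between 9.5 and 9.0. These figures rest on assumed rates, independence of the two events, 84 patients per arm and both arms being in the safety set. With no leukocytosis the loss is nil; if leukocytosis is commoner on MMF, power can rise.

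This is a minor point: an inexpensive improvement in reporting, with no bearing on the primary efficacy analysis.

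**What to change.** In SAP 6.4.1 and protocol 7.7, list leukopenia and leukocytosis as two separate items, each reported with its own number and proportion of patients by arm. The cost is one extra table row. Haematology is already collected and adverse events are already coded, so no data collection or trial procedure changes.
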